**Title:** Soy isoflavones and cholecalciferol for treatment of irritable bowel syndrome: study protocol for a 2× 2 factorial, randomized controlled trial

**Abstract**

**Background**

Irritable bowel syndrome is a common functional gastrointestinal disorder especially in women and there are insufficient high quality and effective clinical trials in this field. This study aims to investigate the interaction and main effects of soy isoflavones and cholecalciferol on symptoms severity, quality of life, total score, and inflammatory markers and gut hyperpermeability in women with IBS.

**Methods/ design**

This study is a factorial randomized controlled trial with 120 eligible patients with IBS that randomly assigned to 4 groups to take soy isoflavones, cholecalciferol or both or none of them in each group for 6 weeks. The follow up session will be at week 10. The primary outcome is symptoms severity and the secondary outcomes are quality of life, total score of disorder, levels of inflammatory markers in serum and blood cells, and the activity of fecal serine protease. The adverse events will be recorded during all sessions of this trial. This study has been approved by Ethics committee in National Nutrition and food Technology Research Institute (NNFTRI) and Digestive Diseases Research Institute (DDRI) in Tehran University of Medical Sciences (TUMS). The ethics committee code is 050459. The findings of this study will contribute to achieve novel effective and safe treatments.

**Discussion:** Up to our knowledge, it will be the first factorial RCT of the impact of soy isoflavones and vitamin D on symptoms severity, QOL, total score, inflammatory markers and fecal serine protease activity in IBS.

**Trial registration:** NCT02026518, clinical trials.gov

**Key words:** Irritable bowel syndrome, Nutrition, Vitamin D, Soy isoflavones, randomized clinical trial

**Background**

Irritable bowel syndrome (IBS) is functional dyspepsia with an epigastric discomfort ([1](#_ENREF_1)). The pathogenesis of this disorder has not clarified yet ([2](#_ENREF_2)). There is an evidence based relationship between symptoms pattern with menstrual cycle in women ([3](#_ENREF_3)). The hypersensitivity and epigastric pain in women with IBS can be due to low activity periods of ovarian hormones before menses ([4](#_ENREF_4)), so ovarian steroids or similar compounds can delay the onset of pain, functional disorder and colonic hyperpermeability in women with IBS ([5](#_ENREF_5)). Furthermore, the estrogen receptors β (ER-β) are expressed predominantly in intestinal mucosa ([4](#_ENREF_4), [6](#_ENREF_6)) and their activity can be modified by estrogen like compounds. Phytoestrogens such as soy isoflavones are similarly structured to ovarian estrogens and can imitate their functions on intestinal mucosa ([7](#_ENREF_7)). In addition, anti- inflammatory bioactive compounds can soothe the inflammatory process and decline the symptoms severity in IBS. The altered food intake in patients with IBS triggers deficiency of some nutrients that can result in aggravation of pain and hypersensitivity ([8](#_ENREF_8)). The active metabolite of vitamin D can modulate the ERs in intestinal smooth muscles, so it can be effective in treatment of symptoms in IBS ([9](#_ENREF_9)). Intestinal hyperpermeability is one of the possible mechanisms of pathogenesis of IBS that aggravate the pain and flatulence occurrence in patients and luminal serine protease can be a relevant marker of pathology of IBS ([10](#_ENREF_10)). Emotional stress can induce higher protease activity in colon and develop more severe symptoms of IBS ([11](#_ENREF_11)). The Quality of life (QOL) impaired significantly in patients with IBS ([12](#_ENREF_12)). Poor QOL in IBS results in high economic loss due to several days of absence of work ([13](#_ENREF_13)). Suppression of symptoms of gastrointestinal dysfunction can contribute to improve QOL ([14](#_ENREF_14)). Nevertheless the prevalence of IBS is high among gastrointestinal disorders and in a recent paper, the prevalence of IBS has been reported between 10 to 20 % ([15](#_ENREF_15)), there are rare high quality RCTs in this field. Moreover, in accordance with the similar functions of soy isoflavones with vitamin D on intestinal mucosa, we could not find any relevant RCT, so to best of our knowledge, this factorial RCT is the first clinical trial on the interaction effect and the main effects of phytoestrogens and vitamin D on symptoms, QOL and gut permeability in women with IBS.

**Methods/ Design**

**Objectives**

The primary objective of this study is to evaluate the main effects and interaction effect of them on IBS severity scores and collect the preliminary data on feasibility and efficacy of these intervention for future larger RCTs in patients with IBS.

**Design**

This study is a double blinded RCT with factorial design. The study will be conducted in endoscopy clinic, Shariati Hospital, Tehran, Iran. This protocol has been approved by Ethics committee in National Nutrition and food Technology Research Institute (NNFTRI) and Digestive Diseases Research Institute (DDRI) in Tehran University of Medical Sciences (TUMS), Tehran, Iran. Written informed consent will be got from all participants after oral and written explanation about the procedure of the study.

The participants that enter to this study will be selected according to eligibility criteria and will be randomized by computerized block randomization method with block size of 6 and will take the intervention for 6 weeks. The participants will be followed up at week 10 (Fig. 1). The assigned four groups will be placebo of vitamin D and placebo of soy isoflavones (P+P), placebo of vitamin D and soy isoflavones (P+S), vitamin D and placebo of soy isoflavones (D+P), vitamin D and soy isoflavones (D+S). The capsule of soy isoflavones contains 10 mg of diadzein, 8.5 mg of genstein and 1.5 mg of glycetin that will be taken twice per day. The vitamin D pearl consists of 50000 IU cholecalciferol that will be taken one per 15 days.

The control group will be obtained by use of placebo of soy isoflavones or cholecalciferol instead of original pill. The placebo of each treatment is in the same color and size.

**Eligibility criteria**

**Inclusion criteria**

Age 18-75 yrs; patients with IBS according to ROME III criteria ([16](#_ENREF_16)); Body Mass index (BMI) 18-25; no intestinal organic diseases; no intestinal infection; no history of chronic gastrointestinal and colorectal diseases; no intestinal major surgery; no regular use of antibiotics, anti-constipation and anti-diarrhea, immune suppressors, metocloperamide, cisaperide, difenoxilate, opium and non-steroidal anti-inflammatory drugs; no pregnancy and lactation; not athlete or bed rest; no history of breast cancer in herself or her family; no severe psychosis

**Exclusion criteria**

Use of soy isoflavones or vitamin D one year before the study; use of soy milk or soy nuts during study; diet changes during study; use of artificial sweetener 2 days before study; no desire to complete the study; adverse effect of supplement; pregnancy during study

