**Outcome Measures**

**Primary outcome**

The severity of symptoms is the primary outcome of this protocol that will be assessed by validated IBS symptoms Severity Score (IBS- SSS) questionnaire at week 0 and week 6. IBS-SSS consists of 5 items on abdominal discomfort, its frequency, flatulence, satisfaction after defecation and interactive impact of IBS on the everyday life. This questionnaire will be filled by interview as VAS and the total score will be between 0 and 500 ([17](#_ENREF_17)).

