**Statistical Analysis**

All data will be analyzed by SPSS version 20 statistical package. The levels of significance will be considered at P lower than 0.05. Intention to Treat (ITT) will be applied for all primary and secondary outcomes data. Quantitative data will be reported as mean (SD) or (SEM), qualitative data will be reported as frequency (percent). Baseline data will be analyzed by ANOVA, Fisher’s exact test or X^2^ test. Linear regression models will be used to analyze the interaction effect and the main effects.

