**Safety**

Any unfavorable reported symptoms will be recorded in specific forms and 4 weeks after cessation of intervention, all the remained will be asked about the compliance of intervention, personal attitude on this study and any adverse events will be reported even in follow up period.

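### The exclusion criteria include events after randomisation, which conflicts with the promised ITT analysis and leaves week-6 follow-up of the removed women unassured

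*Protocol*

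**What the plan says.** The Design section sets the order of events. Women are selected on the eligibility criteria, then "will be randomized by computerized block randomization method with block size of 6 and will take the intervention for 6 weeks".

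The Exclusion criteria section puts two kinds of item in one list. Some refer to the time before the study, such as supplement use in the preceding year. Others refer to the trial itself: "use of soy milk or soy nuts during study; diet changes during study" and "no desire to complete the study; adverse effect of supplement; pregnancy during study". The Inclusion criteria already require that a woman is not pregnant at entry.

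On the analysis population, the Statistical Analysis section says: "Intention to Treat (ITT) will be applied for all primary and secondary outcomes data". It does not define the set further.

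Under Primary outcome, IBS-SSS is taken by "questionnaire at week 0 and week 6. IBS-SSS consists of 5 items", so the single post-baseline measurement is at week 6.

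On safety, the abstract says: "The adverse events will be recorded during all sessions of this trial". The Safety section has reported symptoms entered on forms. Four weeks after treatment ends, "all the remained will be asked about the compliance of intervention"; the same sentence goes on to personal attitude and to adverse events, including those in the follow-up period.

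**The concern.** An exclusion criterion decides who is in the trial. When its trigger can occur only after allocation, it decides who is kept, and that decision can depend on the assigned treatment and on how the woman is doing. Intention-to-treat analysis exists to prevent such selection. A reader of the Exclusion criteria would drop a woman who had an adverse effect of the supplement; a reader of the Statistical Analysis section would keep her. Two teams following the same protocol could therefore analyse different populations for the primary outcome.

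The damage also occurs before the analysis. If a removed woman is not seen at week 6, she has no post-baseline IBS-SSS. Calling the analysis ITT does not supply the missing value, and no later analysis plan can recover it. The Discussion itself expects that loss to follow-up may be large in IBS trials.

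**Working it through.** **Step 1: which items follow randomisation.**

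- Adverse effect of the supplement: clearly after, because the Design section places intake after randomisation.
- Pregnancy during the study: after entry in practice, because the Inclusion criteria screen for it at entry.
- Soy foods or diet changes during the study: mostly after. The Discussion mentions data checks at week -1, so some cases could be seen before treatment.
- No desire to complete: could be judged at screening, but in practice also arises later.

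The first two are enough to establish the conflict.

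**Step 2: is there a reconciling statement?** Read together, the Exclusion criteria, Statistical Analysis and Safety sections do not say that the during-study items only stop treatment, that removed women stay in follow-up, or that they are analysed.

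**Step 3: the plan's own figures.** The plan gives no rate of removal by arm. The related figures are 21 per group before dropout, a 15% dropout allowance, 30 per group and 120 in total. Inflating 21 for 15% gives 21/(1 − 0.15) = 24.7, that is 25, not 30. This is a separate matter and nothing here rests on it. A dropout allowance protects precision; it does not remove selection bias.

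**Step 4: illustration of size.** With four groups of 30, each factor's main effect compares 60 with 60. Assume no true effect and unit SD. Let p be the proportion removed in an arm, and let removed women be k SD worse than retained women in both arms. If the whole arm has mean 0 (higher is worse), the retained women have mean −p·k. The difference between retained groups is then

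bias = −(p_active − p_placebo)·k,

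with SE = √(1/[60(1 − p_active)] + 1/[60(1 − p_placebo)]). By normal approximation, the true two-sided type I error is Φ(−1.96 + |bias|/SE) + Φ(−1.96 − |bias|/SE).

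Example with 15% v 5% and k = 1: bias = −(0.15 − 0.05)·1 = −0.10. The numbers retained are 60 × 0.85 = 51 and 60 × 0.95 = 57. SE = √(1/51 + 1/57) = 0.193, and 0.10/0.193 = 0.519. The error is Φ(−1.441) + Φ(−2.479) = 0.075 + 0.007, about 8.1% before rounding of the parts.

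| Removed, active v placebo | k | Spurious benefit (SD) | True alpha |
|---|---|---|---|
| 10% v 5% | 0.5 | 0.025 | 5.2% |
| 10% v 5% | 1 | 0.05 | 5.8% |
| 15% v 5% | 0.5 | 0.05 | 5.8% |
| 15% v 5% | 1 | 0.10 | 8.1% |
| 20% v 5% | 0.5 | 0.075 | 6.7% |
| 20% v 5% | 1 | 0.15 | 11.9% |
| 15% v 15% | 0.5 or 1 | 0 | 5.0% |

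All rates and values of k are assumed. If placebo loses more women, the sign reverses. The table treats both groups that receive a factor alike; if only one of the two is affected, the shift in that factor's main effect is roughly halved.

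**The case against.** The strongest reply is that the two sections address different things. The Exclusion criteria never mention the analysis set, whereas the Statistical Analysis section does. The during-study items could be meant as reasons to withdraw from treatment, with ITT governing the analysis, and the detail of the ITT set is commonly left to the SAP. That reading is possible, so a reader should not infer that the two rules can never be reconciled. But the protocol calls the items exclusion criteria and nothing in it supports the kinder reading. Whether removed women are seen at week 6 is also a matter of conduct, which an SAP cannot settle afterwards.

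Three stronger readings are tempting and are not supported:

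- A reader might infer that all five during-study items can only follow randomisation. As shown in step 1, some could be judged earlier.
- A reader might infer that efficacy will be overstated. The direction is not fixed. If women who do not improve lose the wish to continue, placebo may lose more of them, which would work against the treatments.
- A reader might take "all the remained will be asked about the compliance of intervention, personal attitude on this study and any adverse events" to mean that the adverse event rate must be understated. The sentence continues by saying that events in the follow-up period are reported too, and events are recorded at every session and as they are reported. A woman removed for an adverse effect has an event the team already knows of. What remains is narrower: the week-10 contact is worded for those still in the trial, so later safety follow-up of removed women is not assured.

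**Conclusion.** The point holds and should be fixed. At least two exclusion criteria act after randomisation. Removing women on them conflicts with the promised ITT analysis, and no statement keeps these women in follow-up for the primary endpoint. This follows from the text alone.

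The size of any bias is a risk, not an established fact. Under the assumptions above it ranges from about 0.03 to 0.15 SD, with a true two-sided alpha of about 5.2% to 11.9%. It is zero if removal is unrelated to arm and outcome. The protocol gives no SD for IBS-SSS, so the shift cannot be put in score points without a further assumption. The safety consequence is secondary and limited to later follow-up.

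**What to change.** Reconcile the Exclusion criteria, Statistical Analysis and Safety sections as follows.

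1. Limit the exclusion criteria to conditions assessed before randomisation.
2. Put the during-study events in a separate list of protocol deviations or reasons for stopping the intervention. Which events stop treatment remains a clinical rule for the investigators.
3. State that every randomised woman is followed where she consents, whatever her adherence, with IBS-SSS sought at week 6 and adverse events at weeks 6 and 10, and that she is analysed in the group to which she was randomised.
4. Reword the week-10 safety contact so that it covers all randomised women, not only those still in the trial.
5. Use the deviation list only to define a supplementary per-protocol analysis.

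The cost is protocol wording and a few extra contacts at visits already scheduled. The sample size does not change. Estimates may be slightly diluted by women who stopped treatment.

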**Outcome Measures**

**Primary outcome**

The severity of symptoms is the primary outcome of this protocol that will be assessed by validated IBS symptoms Severity Score (IBS- SSS) questionnaire at week 0 and week 6. IBS-SSS consists of 5 items on abdominal discomfort, its frequency, flatulence, satisfaction after defecation and interactive impact of IBS on the everyday life. This questionnaire will be filled by interview as VAS and the total score will be between 0 and 500 ([17](#_ENREF_17)).

**Secondary outcomes**

QOL in IBS will be assessed by validated IBS- QOL questionnaire at week 0 and week 6. IBS- QOL questionnaire has 34 items on dysphoria (8 items), body image (4 items), health-oriented worries (3 items), sexual related worries (2 items), social behavior (4 items), intervene with every-day activity (7 items) and personal relationship (3 items) ([18](#_ENREF_18)). Total score of IBS, another secondary outcome will be determined by a VAS between 0 and 100 –mm to evaluate the effect of interventions on total severity of IBS at week 0, week 6 and week 10 (follow up)([17](#_ENREF_17)).

Fecal serine protease enzyme activity is the marker for gut hyperpermeability, as one of the secondary outcomes will be measured by enzyme- linked immunosorbant assay (ELISA) kit after collection of fecal samples, keep them in -80◦ C freezer and preparation by 5 ml Tris buffer and centrifuged in 3000 RCF for 10 min.

Ten ml fasting venous blood samples will be taken from all participants that separated in 3 microtubes: 1- a microtube with EDTA as anti-coagulant will be centrifuged at 3000 RCF for 10 min to separate plasma and whole blood. 2- a microtube without any type of anti-coagulants will be kept for 30 min at room temperature, then will be centrifuged at 3000 RCF for 10 min to separate serum. 3- a microtube with heparin as anti-coagulant will be used to separate PBMC and culture them followed by centrifuging at 2000 RCF for 15 min. Isolated PBMC will be used to compare the amount of Nuclear Factor κβ (NF- κβ) before and after the intervention. All separated samples will be collected quickly in crayotubes and will be transferred to -80◦ C freezer until experiments start. Sera will be recovered to determine the level of serum 25- OH vitamin D and Tumor Necrosis factor- α (TNF- α) at week 0 and week 6.

**Statistical Methods**

**Sample Size**

According the factorial design, we consider required sample size to compare soy isoflavones group versus control group and vitamin D group versus control group, then the maximum predicted value is considered as final required sample size to assess the efficacy of the interaction effect and the main effects. A similar study ([19](#_ENREF_19)) is used to determine the sample size by T test to compare the means of QOL. The probability of type 1 error is 5% and the probability for type 2 error is 20%, so the calculated sample size is 21 persons per each group. The G power software version 3-1-7 is used to calculate sample size. The probability of dropout is considered 15%, so the predicted number increases to 30 for each group and we will require 120 patients with IBS. This number of patients is sufficient to find the interaction effect as 2 times of main effects, although we will need more sample size if we desire to find much smaller scale of differences.

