**Discussion**

Up to our knowledge, it will be the first factorial RCT of the impact of soy isoflavones and vitamin D on symptoms severity, QOL, total score, inflammatory markers and fecal serine protease activity in IBS. This study will be investigated to determine the efficacy of two interventions or their any probable synergistic effect on IBS.

IBS-SSS, IBS-QOL and total score will be recorded by face to face interview and similar training sessions will be held for all research team to reduce the information and selection bias and inter-individual variability among the interviewers.

The step by step manual for laboratory analysis will be provided to prevent any random error in long duration of investigations. Furthermore, all analyses will be done at research lab of DDRI to control any systematic error of lab systems and technicians.

The strength points of this study can be the following items: Vitamin D deficiency is prevalent in our country especially in Tehran because of the latitude of this city and the impact of air pollution, Moreover there is enough evidence on the deficiency of vitamin D especially in women with IBS, so we select the women with IBS that reside in Tehran. Data management will be done at -1 week, week 0, week 6 and week 10 by manually checking of data accuracy and relevancy by one the members of research team. Furthermore, the statistician will clean all data after entrance of all data in statistical software and will report any unreal data to data collection members to check again.

The amount of TNF-α and NF- κβ is a critical marker of mild inflammation level in IBS and the effect of intervention can be critical for future RCTs. Fecal serine protease is an acceptable and feasible marker for intestinal permeability that is safe and with the minimum offensive consequence on the intestinal tissues compared to biopsy samples of intestine during colonoscopy ([20](#_ENREF_20)).

This study can contribute to specify the marginal means of soy isoflavones and vitamin D and any interaction effect of them on clinical and biological outcomes in IBS ([21](#_ENREF_21)). The potential possibility of large lost to follow up in most clinical trials on IBS makes this clinical research inexplicit to report any realistic findings while it can be assuring to evaluate the efficacy and safety of the interventions in IBS for future larger population based RCTs.

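### A 15% dropout allowance turns 21 per group into 25, not 30, so the three figures behind the total of 120 do not agree

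*Protocol*

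**What the plan says.** The protocol's Sample Size section sizes two comparisons by t-test on mean quality of life, soy isoflavones against control and vitamin D against control, and takes the larger number. It sets the error rates ("The probability of type 1 error is 5"% and "the probability for type 2 error is 20"%) and reports a single result: "so the calculated sample size is 21 persons per each group". It then goes from this base to the enrolment target in one sentence: "The probability of dropout is considered 15%, so the predicted number increases to 30 for each group", and hence to 120 patients. The Abstract repeats 120 patients in four groups.

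No effect size, standard deviation or sidedness is given. No rounding rule, reserve or second inflation is mentioned between 21 and 30. The closing remark of the section, on the size of interaction that can be found, comes after the 120 and is not offered as a reason for it.

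**The concern.** The sentence presents 30 as the consequence of a 15% dropout allowance applied to 21. A reader who repeats the step gets 25. The gap is too large for rounding, and it sits in the figure that fixes enrolment.

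What is at stake is the credibility of the sample size justification and the attrition the trial was planned to absorb. If 21 is the number needed, 120 randomised can lose far more than 15%. If 15% is the planned loss and 30 is right, the base was not 21. These describe different designs, and the protocol states parts of both.

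**Working it through.** **Inputs, all from the protocol's Sample Size section.** Base n = 21 per group; dropout = 15%; stated result = 30 per group and 120 in total; type 1 error 5%; type 2 error 20%. There are four equal groups (4 × 30 = 120). The dropout step takes 21 as given, so the missing effect size does not affect it.

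**Step 1. Attempt to reproduce 30.**
- Usual formula, n/(1 − d): 21/0.85 = 24.7, rounded up to 25; 4 × 25 = 100.
- Common shortcut, n × (1 + d): 21 × 1.15 = 24.15, rounded up to 25; again 100.
- Inflating the total of 4 × 21 = 84: 84/0.85 = 98.8, rounded up to 99; or 84 × 1.15 = 96.6, rounded up to 97.

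None gives 30 or 120. The excess is 30 − 25 = 5 per group and 120 − 100 = 20 in total, 20% above what the stated inputs yield.

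**Step 2. Does the randomisation explain it?** The Design section gives a block size of 6. The next multiples of 6 above 100 are 102 and 108, and 108 also divides equally by four. Block rounding does not lead to 120.

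**Step 3. Which inputs would give 30?**
- 21/(1 − 0.30) = 30.0: the stated base with twice the stated dropout.
- 25/0.85 = 29.4, rounded up to 30; or 26 × 1.15 = 29.9, rounded up to 30: the stated dropout with a larger base.
- 21/0.85² = 29.07, rounded up to 30: the 15% allowance applied twice.

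The protocol describes none of these routes, and its text cannot separate them.

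**Step 4. Direction of the error.** 30 × 0.85 = 25.5, so about 25 per group remain after 15% loss, against 21 required. The loss that brings 30 down to 21 is 1 − 21/30 = 30%.

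**Step 5. What this means for power, under assumptions.** I back-solved the standardised difference d from the two-group t-test at 5%. Neither d nor sidedness is stated, so a range is needed. Two cases bound the rounding: power exactly 80% at 21 per group, or 21 as the result of rounding up from just above 20 (in the limit, 80% at 20 per group).

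| Assumption | d | Power at 21 | Power at 25 | Power at 25.5 |
|---|---|---|---|---|
| Two-sided, 80% at 21 | 0.886 | 80.0% | 86.6% | 87.3% |
| Two-sided, 80% at 20 | 0.909 | 82.0% | 88.3% | 88.9% |
| One-sided, 80% at 21 | 0.781 | 80.0% | 85.9% | 86.5% |
| One-sided, 80% at 20 | 0.801 | 81.7% | 87.4% | 88.0% |

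So if 21 is the right base, power at 15% loss is about 86% to 89%. This is the power of the protocol's own calculation, a comparison of two groups on quality of life.

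**The case against.** The best defence is that no harm is done. Enrolling 120 exceeds what 21 per group with 15% loss requires, extra patients protect against worse attrition, and neither the analysis nor its validity changes. All of that stands. It limits the consequence to the justification of the number, but it does not make the sentence correct.

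A second defence is that 21 could be the slip. Two comparisons were sized and only one result is reported, and a base of 25 or 26 would make 15% and 30 consistent. That is possible and cannot be checked, because no effect size or standard deviation is given. It is a reason not to declare any one figure the culprit.

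Two stronger readings are tempting, and the protocol supports neither.
- *The planned dropout was really 30%.* That 21/0.70 is exactly 30 is suggestive, and the Discussion mentions "The potential possibility of large lost to follow up in most clinical trials on IBS". But that remark concerns IBS trials in general, speaks of a possibility and gives no rate. It does not replace the stated 15%, and other routes also reach 30.
- *The trial's power is misstated to its disadvantage.* If 21 and 15% are both right, power for the sized comparison is above 80%, not below. Nor are 80% or 87% the power of the trial. Quality of life is a secondary outcome, the primary outcome is IBS-SSS, and the planned analysis is linear regression for main effects and interaction.

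**Conclusion.** The point holds as an arithmetic inconsistency. From 21 per group and 15% dropout the enrolment is 25 per group and 100 in total; the protocol states 30 and 120. This conclusion needs no assumption beyond the figures printed in the Sample Size section, and both usual inflation formulas agree on it.

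Which of 21, 15% or 30 is wrong cannot be determined from the protocol. The error lies on the safe side and creates no shortfall at this step. The power range in the working rests on 21 being the right base and giving about 80% to 82%; it says nothing about IBS-SSS or the interaction.

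**What to change.** Keep 120 and make the three figures agree, by whichever of these is true:
- correct the base number, if the larger of the two comparisons gave about 25 rather than 21;
- correct the dropout rate, if 30% was the allowance;
- keep 21 and 15%, and give the reason for the 20 patients beyond 100.

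If 21 per group is confirmed as the requirement, add that 120 randomised tolerates up to 30% attrition. Any power figure added should be labelled as that of the two-group quality-of-life t-test, with the effect size and sidedness used, and not as the power for IBS-SSS or the interaction.

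The cost is a sentence or two in the Sample Size section, with no change to enrolment, randomisation or analysis.
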